### Sample Size Calculations

Postdischarge acute hospital care and index hospital LOS are coprimary outcomes with a shared α. We allocate α=.04 for acute hospital care and α=.01 for index hospital LOS (details in Multimedia Appendix 6).

Table 1 presents the trial power for acute hospital care based on a log-rank test with a 2-sided α of .04 using SAS software (version 9.4; SAS Institute Inc). Assuming a 14% event rate in the control group, with an overall sample of size 2500 participants (1250 in the control group and 1250 in the treatment group), we will achieve 88.7% power to detect a relative risk reduction of at least 0.70 (30% relative risk reduction). Table 2 presents the trial power for index LOS based on a 2-sample Wilcoxon test assuming equal variance with a 2-sided α of .01. We expect patients in the standard care group to have a mean index hospital LOS of 2.5 days. If the knowledge that patients in the intervention group will receive virtual care with RAM after hospital discharge results in 35% of patients having their index hospital LOS reduced by 1 day, we will require a sample size of 2500 to have more than 80% power to detect this difference, with a 2-sided α of .01.

**Table 1 table1:** Power to detect an RR^a^ (0.65, or 0.70, or 0.75) based on log-rank test with a 2-sided α of .04 assuming control group event rates 12%, 14%, 16%, and 18% for a given total sample of size 2500, 2800, 3000, or 3200.

Sample size per group			RR 0.65 (35% reduction)							RR 0.70 (30% reduction)							RR 0.75 (25% reduction)				
			Assumed control event rate (%)		Treatment P (%)		Power (%)		Assumed control event rate (%)			Treatment P (%)		Power (%)		Assumed control event rate (%)			Treatment P (%)		Power (%)
**2500**			12		7.8		—^b^		12			8.4		—		12			9		—
	1250	—		—		93.3		—			—		82.5		—			—		65.5	
	1400	—		—		95.6		—			—		86.7		—			—		70.6	
	1500	—		—		96.7		—			—		89.0		—			—		73.7	
	1600	—		—		97.6		—			—		90.1		—			—		76.5	
**2800**			14		9.1		—		14			9.8		—		14			10.5		—
	1250	—		—		96.6		—			—		88.7		—			—		73.4	
	1400	—		—		98		—			—		92		—			—		78.3	
	1500	—		—		98.6		—			—		93.6		—			—		81.1	
	1600	—		—		99		—			—		95		—			—		83.6	
**3000**			16		10.4		—		16			11.2		—		16			12		—
	1250	—		—		98.4		—			—		93		—			—		80	
	1400	—		—		99.1		—			—		95.4		—			—		84.4	
	1500	—		—		99.4		—			—		96.5		—			—		86.8	
	1600	—		—		99.6		—			—		97.4		—			—		88.9	
**3200**			18		11.7		—		18			12.6		—		18			13.5		—
	1250	—		—		99.3		—			—		95.8		—			—		85.3	
	1400	—		—		99.7		—			—		97.4		—			—		89.1	
	1500	—		—		99.8		—			—		98.2		—			—		91.1	
	1600	—		—		99.9		—			—		98.7		—			—		92.8	

^a^RR: relative risk.

^b^Not applicable.

**Table 2 table2:** Power calculation based on 2-sample Wilcoxon tests assuming equal variance in LOSa with a 2-sided α of .01.

Standard care group expected index hospital LOS (days)	Intervention group expected impact on index hospital LOS	Sample size, n		
		80% power	85% power	90% power
3	40% of patients have their LOS reduced by 1.5 days	1078	1216	1400
3	35% of patients have their LOS reduced by 1.5 days	1450	1634	1882
3	30% of patients have their LOS reduced by 1.5 days	2030	2288	2634
3	40% of patients have their LOS reduced by 1.0 days	2618	2950	3396
3	35% of patients have their LOS reduced by 1.0 days	3482	3924	4518
3	30% of patients have their LOS reduced by 1.0 days	4826	5438	6260
2.5	40% of patients have their LOS reduced by 1.5 days	714	806	928
2.5	35% of patients have their LOS reduced by 1.5 days	968	1090	1256
2.5	30% of patients have their LOS reduced by 1.5 days	1362	1536	1768
2.5	40% of patients have their LOS reduced by 1.0 days	1764	1988	2290
2.5	35% of patients have their LOS reduced by 1.0 days	2356	2656	3058
2.5	30% of patients have their LOS reduced by 1.0 days	3280	3696	4254
2	40% of patients have their LOS reduced by 1.5 days	424	478	552
2	35% of patients have their LOS reduced by 1.5 days	582	656	754
2	30% of patients have their LOS reduced by 1.5 days	828	932	1074
2	40% of patients have their LOS reduced by 1.0 days	1078	1216	1400
2	35% of patients have their LOS reduced by 1.0 days	1450	1634	1882
2	30% of patients have their LOS reduced by 1.0 days	2030	2288	2634

^a^LOS: length of stay.

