### Randomization

Randomization occurs before surgery, after eligibility is confirmed, and informed consent is obtained. We randomize as close to the time of surgery as possible to minimize the risk of surgery postponement. Patients are randomized using an Interactive Web Randomization System, a 24-hour computerized system maintained by the coordinating center at the Population Health Research Institute, a joint institute of Hamilton Health Sciences and McMaster University in Hamilton, Ontario, Canada.

The randomization process uses block randomization with varying block sizes stratified by site, ensuring that study personnel and investigators remain unaware of block sizes. Patients are randomized in a 1:1 ratio to receive VC-RAM or standard care. Following randomization, research personnel notify the patient’s surgeon and the patient of the treatment allocation. Patients, health care providers, and data collectors are aware of treatment assignments, while outcome adjudicators remain blinded to treatment allocation.

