PVC-RAM-3 trial is powered to detect a 30% relative risk reduction in acute hospital care and a 1-day reduction in index LOS in at least 35% of patients. With estimated baseline rates of 20%-25% for acute hospital care and an average hospital stay of 2.5 days [7], a 30% reduction could prevent 6-7.5 acute care visits per 100 patients. Postpandemic elective surgery volumes for those meeting PVC-RAM-3 inclusion criteria is approximately 4500 surgeries per year. If we reduce the LOS by a day for 30% of these elective surgeries, we could free up hospital beds and increase surgical volume by an additional 1350 cases per year to address surgical backlogs. This has the potential to generate substantial cost savings for the health care system.

Our previous trial demonstrated the potential of VC-RAM to improve other patient-important outcomes, such as the identification and correction of drug errors, pain management, and the medical optimization of patients, including those with atherosclerotic disease, for whom proven secondary prevention therapies exist, and those who smoke tobacco [8]. However, significant opportunities remain to further optimize pharmacological therapy to enhance long-term health outcomes, and these are evaluated in PVC-RAM-3.

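### The length-of-stay power in Table 2 was computed for a 14% lower mean in an exponential distribution, not for the stated equal-variance effect of 35% of patients losing 1 day

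*Protocol article*

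**What the plan says.** The protocol article describes the LOS calculation in three places.

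- **Sample Size Calculations, text.** "Table 2 presents the trial power for index LOS based on a 2-sample Wilcoxon test assuming equal variance with a 2-sided α of .01". The control assumption follows: "We expect patients in the standard care group to have a mean index hospital LOS of 2.5 days". The effect is that knowing the allocation "results in 35% of patients having their index hospital LOS reduced by 1 day, we will require a sample size of 2500", and the promise is "to have more than 80% power to detect this difference, with a 2-sided α of .01".
- **Table 2.** The title repeats the Wilcoxon test, equal variance and two-sided .01. Each row gives an effect as a share of patients losing a fixed number of days. The planning row, at a control mean of 2.5 days, is "35% of patients have their LOS reduced by 1.0 days", with total N of 2356, 2656 and 3058 for 80%, 85% and 90% power.
- **Discussion, Overview.** The trial is said to be powered for "a 1-day reduction in index LOS in at least 35% of patients".

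The article gives no SD and no distribution for LOS. It refers to Multimedia Appendix 6 for sample size details, which is not shown. The planned LOS analysis (Statistical Analyses) is also the Wilcoxon rank sum test.

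**The concern.** In Table 2, the rows for a 3-day mean with a 1.5-day cut and for a 2-day mean with a 1.0-day cut are identical at every share and power. At 40%, both give 1078/1216/1400. The mean falls differ (0.60 and 0.40 day) but the ratio of means is 0.80 in both. So N follows the ratio of means, not the number of days lost. This points to a scale model rather than a fixed-day cut in some patients.

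The Wilcoxon test responds to how often an intervention stay is shorter than a control stay, not to the mean difference. The same mean fall of 0.35 day can give very different power, depending on which patients leave earlier. If the table was built on another effect, the power claim does not describe the effect that the article names. A reader of a null LOS result could then take 1 day in 35% of patients as ruled out, on a calculation never made for it.

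**Working it through.** **Inputs.** Control mean m, share f and days d from each row of Table 2; allocation from Randomization ("Patients are randomized in a 1:1 ratio to receive VC-RAM or standard care"); two-sided α = .01 as stated, with .02 as the alternative.

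**1. Reproduce the printed figures.** Take control LOS as exponential with mean m, intervention LOS as exponential with mean m − f × d, and r as the ratio of means. Then:

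- p = P(control stay longer) = 1/(1 + r)
- v = 2(A − p²) + 2(B − p²), with A = 1 − 2r/(1 + r) + r/(r + 2) and B = 1/(1 + 2r)
- θ = ln[p/(1 − p)] = −ln r; σ0 = √(16/3) = 2.3094; σ1 = √v / [p(1 − p)]
- N = [(z_α σ0 + z_power σ1)/θ]², rounded up to an even number

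Planning row: r = (2.5 − 0.35 × 1)/2.5 = 2.15/2.5 = 0.86; p = 1/1.86 = 0.5376; A = 0.3760; B = 0.3676; v = 0.3310; σ1 = 2.3145; θ = 0.1508.

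- At two-sided .02 (z = 2.3263), 80% power: N = [(2.3263 × 2.3094 + 0.8416 × 2.3145)/0.1508]² = 2355.8, so 2356. For 85% and 90%: 2656 and 3058. All three equal the printed values.
- At the stated two-sided .01 (z = 2.5758): 2742, 3064 and 3494.

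Over the whole table, 54 of 54 cells match to the patient at two-sided .02 and 0 of 54 at two-sided .01.

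**2. A check on α that needs no LOS model.** With equal variance, N for 90% over N for 80% is [(z_α + 1.2816)/(z_α + 0.8416)]². This is 1.274 at two-sided .01 and 1.297 at .02. The printed ratio is 3058/2356 = 1.298.

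**3. What the matching model implies.** An exponential SD equals its mean, so the SDs are 2.5 and 2.15 days, which are not equal. The effect is a 14% reduction in scale. The control distribution has 1 − e^(−0.4) = 33% of stays under 1 day, and those cannot be cut by a full day.

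**4. Power at N = 2500, two-sided .01, on that exponential base.**

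- *Modelled effect:* Φ[(√2500 × 0.1508 − 2.5758 × 2.3094)/2.3145] = Φ(0.688) = 75%.
- *Random 35% lose 1 day, floored at 0:* p = 0.65 × 0.5 + 0.35 × (1 − 0.5e^(−0.4)) = 0.5577. Power = Φ[√(3 × 2500) × 0.0577 − 2.5758] = 99%. Drawing the same number of patients only from stays over 1 day also gives about 99% by simulation.
- *Longest-staying 35% lose 1 day:* p = 0.5301. Power = Φ[86.60 × 0.0301 − 2.5758] = 51%, confirmed by simulation.

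**5. Dependence on the assumed shape.** For the longest-stayer case with gamma LOS of mean 2.5 days (an assumption), power is about 80% at CV 0.8 and about 98% at CV 0.6. For a literal equal-variance normal shift of 0.35 day at N = 2500 and two-sided .01, power is 99.9%, 95.5%, 80.1% and 60.8% for assumed SDs of 1.5, 2, 2.5 and 3 days.

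**The case against.** **The appendix may name the model.** It may. It could then supply the distribution, but it could not make the article's equal-variance and fixed-day wording true of these numbers.

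**The wording may be shorthand for a mean fall of 0.35 day.** This is a fair reading of how the table was built. But the Discussion repeats the effect as a statement about individual patients, and a rank test does not treat equal mean falls alike.

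**An equal-variance model nearly fits.** A normal Wilcoxon calculation at the stated two-sided .01, with SD set to the average of the two arm means and efficiency 0.864, comes within −0.7% to +2.4% of every cell. The identical rows alone do not exclude such a model, because the SD could rise with the mean from row to row. It still does not reproduce the cells exactly and gives the wrong 90%/80% ratio. The exponential model is exact in all 54 with no shape parameter to choose, so it is the better explanation.

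**The promise is a floor.** If a random 35% lose 1 day, 99% is indeed above 80%. This stands, and it limits the finding.

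**Readings that go too far.** A reader might infer that the trial is underpowered for LOS. The 51% figure needs both the exponential shape and a longest-stayer pattern that the article never describes. A reader might also infer that the α split rests on Table 2, but Trial Outcomes attributes it to blinded overall data. Nor do two exponential distributions show that each patient's stay is cut by 14%. They fix the two distributions, not individual effects.

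**Conclusion.** The point holds as a mismatch between the stated effect and the computed one. The calculation behind Table 2 compares exponential LOS with means 2.5 and 2.15 days at two-sided .02. It is neither an equal-variance calculation nor one for 1 day lost by 35% of patients. The identification rests on an exact match in 54 of 54 cells.

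At the stated two-sided .01, the table's own model has 75% power at N = 2500, short of the promised 80%. For the effect as worded, power on the same base runs from about 51% to about 99%, depending on who leaves earlier. The direction is therefore not fixed. The low end depends on the assumed shape, since the documents give no SD. The α discrepancy is a separate fault, and the effect mismatch remains at either level. The power statement should be corrected, but the trial's ability to answer the LOS question is not shown to be deficient.

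**What to change.** - In Sample Size Calculations, Table 2 and the Discussion Overview, state the effect actually powered: exponential LOS, mean 2.5 versus 2.15 days, a ratio of 0.86. Delete the equal-variance wording.
- Give the power for that effect at the stated two-sided .01 (about 75% at N = 2500), and recompute Table 2 at that level.
- If the claim of 1 day in 35% of patients is kept, support it with simulated Wilcoxon power at N = 2500 and two-sided .01, using the blinded pooled LOS distribution. Remove 1 day from 35% of all patients, drawn from those staying longer than 1 day, and report the longest-stayer case as a sensitivity bound. Cutting 35% of the stays over 1 day is a different and smaller effect: on the exponential base it reaches only 0.35 × 67% = 23% of patients.

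The cost is rewording, a recomputed table and one short simulation on data already held, run without treatment codes. Enrolment and the planned analysis do not change. The downside is that a single power figure becomes a range.

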### Statistical Analyses

We will analyze all data according to a prespecified statistical analysis plan developed and finalized before any investigator is unblinded.

Following the intention-to-treat principle, we will analyze patients in the treatment groups to which they were randomized. For both coprimary outcomes, we will compare all patients allocated to the PVC-RAM-3 intervention to all patients allocated to standard care.

For coprimary 1 (composite of hospital readmission or emergency department visit), we will compute the time to event from the discharge date and plot the cumulative incidence curves between the two treatment groups. We will use a Cox regression model to obtain hazard ratios and 95% CIs. Any acute hospital care event that occurs before patients undergo their index surgery, in cases where surgery is postponed, will not be included in this outcome.

For coprimary 2 (index hospital LOS), we will calculate the hospital LOS for both groups and compare them with a 2-sample Wilcoxon rank sum test. Given the large sample size, the 2-sample Wilcoxon rank sum test will produce results that will be similar to the 2-sample *t* test.

For the coprimary outcome analyses, we will censor patients whose surgeries were canceled and not rescheduled within 30 days of randomization.

VC-RAM will be considered effective if either of the 2 coprimary efficacy analyses is significant. We will use a gatekeeping with a fallback procedure to analyze their statistical significance [12]. We will start with an overall α of .05, split between the two outcomes with a computed 2-sided *P* value less than an α of .04 for postdischarge acute hospital care and less than an α of .01 for index length of hospital stay. If the first coprimary outcome achieves significance at an α level of <.04, the α from this test will be added to the second coprimary outcome’s α (ie, the α will be .05). However, if the first coprimary outcome is not significant, the second coprimary outcome will be tested at an α level of <.01.

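### Table 2 is labelled 2-sided α=.01, but its sample sizes fit 2-sided α=.02; on the table's own model, 2500 patients give about 75% power for length of stay, not more than 80%

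*Protocol article*

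**What the plan says.** Under Sample Size Calculations in the protocol article, α is divided between the two coprimary outcomes: "We allocate α=.04 for acute hospital care and α=.01 for index hospital LOS". The text then says "Table 2 presents the trial power for index LOS based on a 2-sample Wilcoxon test assuming equal variance with a 2-sided α of .01", and the table title repeats it: "Power calculation based on 2-sample Wilcoxon tests assuming equal variance in LOSa with a 2-sided α of .01".

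The planning scenario has two parts. For the control mean: "We expect patients in the standard care group to have a mean index hospital LOS of 2.5 days". For the effect, knowledge of the allocation "results in 35% of patients having their index hospital LOS reduced by 1 day". The matching row of Table 2 (2.5 days) reads "35% of patients have their LOS reduced by 1.0 days 2356 2656 3058" for 80, 85 and 90% power. From this the text concludes that "we will require a sample size of 2500 to have more than 80% power to detect this difference, with a 2-sided α of .01".

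Statistical Analyses compares a 2-sided P value for LOS with .01. LOS is tested at .05 if acute hospital care is significant at .04. Otherwise, "if the first coprimary outcome is not significant, the second coprimary outcome will be tested at an α level of <.01".

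**The concern.** The sample sizes in Table 2 rise too steeply from 80% to 90% power for a 2-sided .01 test. A stricter α means a larger critical value, so the step in power has a smaller proportional effect on N. The printed steps fit a critical value for 2-sided .02.

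LOS is a coprimary outcome, and the trial counts as positive if either coprimary is significant, so LOS alone at .01 is a declared route to success. If the power was worked out at twice the α of the test, a non-significant LOS result would be read against a type II error below 20% when the table's own model gives about 25%.

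**Working it through.** **Inputs.** Table 2 total sample sizes; 2-sided α=.01 (text, table title, analysis rule); control mean 2.5 days; 35% of patients × 1 day = 0.35 days, so an intervention mean of 2.15 days; N = 2500, randomized 1:1. The SD and distribution of LOS are not stated.

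**1. The α implied by the table.** With N proportional to (zα + zpower)², effect size and variance cancel in a ratio within a row:

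N90/N80 = [(zα + 1.2816)/(zα + 0.8416)]²

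| | zα | N85/N80 | N90/N80 |
|---|---|---|---|
| Required for 2-sided .01 | 2.576 | 1.117 | 1.274 |
| Required for 2-sided .02 | 2.326 | 1.127 | 1.297 |
| Planning row (2356/2656/3058) | 2.317 | 1.127 | 1.298 |
| Largest-N row (4826/5438/6260) | 2.325 | 1.127 | 1.297 |

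Over all 18 rows, the zα solved from N90/N80 lies between 2.28 and 2.34. Allowing for rounding up to even N, the highest value any row permits is 2.376. The largest-N row, where rounding matters least, allows 2.320 to 2.329. No row reaches 2.576.

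**2. Reproducing the sample sizes.** Rows with the same proportional reduction in the mean have identical N. For example, 3 days with 40% × 1.5 days and 2 days with 40% × 1.0 day are both a 20% reduction, and both give 1078/1216/1400. This fits a scale model for LOS. Assume exponential LOS and use the Noether formula for the Wilcoxon test:

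N = (zα + zpower)² / [3(p − 0.5)²], with p = 2.5/(2.5 + 2.15) = 0.5376

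| Planning row | 80% | 85% | 90% |
|---|---|---|---|
| Table 2 | 2356 | 2656 | 3058 |
| Formula, 2-sided .02 | 2362 | 2661 | 3063 |
| Formula, 2-sided .01 | 2749 | 3071 | 3502 |

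At 2-sided .02, all 54 cells agree to between 4 and 7 patients. A version with separate null and alternative variances gives 2356/2655/3057 for the planning row. At 2-sided .01, every cell is 14 to 18% too high.

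**3. Power with 2500 patients.** Scale the sponsor's own planning row; no LOS distribution is needed here.

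- Noncentrality at N = 2356: 2.326 + 0.842 = 3.168.
- At N = 2500: 3.168 × √(2500/2356) = 3.263.
- 2-sided .01: Φ(3.263 − 2.576) = Φ(0.687) = 75.4%.
- 2-sided .02: Φ(3.263 − 2.326) = 82.6%, which matches the claim of more than 80%.
- 2-sided .05: Φ(3.263 − 1.960) = 90.4%.

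Simulated Wilcoxon tests (5000 runs, exponential means 2.5 and 2.15) at N = 2500 give 75.0, 82.2 and 90.5%.

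**4. Sample size needed at 2-sided .01.** The factor is [(2.576 + zpower)/(2.326 + zpower)]², which is 1.164, 1.154 and 1.143 for 80, 85 and 90% power. Applied to the planning row, it gives about 2742, 3065 and 3496. Simulation at N = 2742 gives 80.4% power.

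**The case against.** The strongest objection is that 75% depends on a model the article never states. Multimedia Appendix 6, which holds the details, is not shown. The scenario described (35% of patients each losing one day) is also not a proportional shift of an exponential distribution. Simulations at N = 2500 and 2-sided .01, with assumed gamma LOS of mean 2.5 and SD from 1.5 to 3, gave power from about 33% to about 100%, depending on the SD and on which patients go home earlier. This stands as a limit on the 75%: it is the power under Table 2's own model, not a model-free fact. It does not rescue the table, because those models are not the one the table uses.

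Secondly, if the variances under the null and the alternative differ, the ratio identifies zα times the ratio of the two SDs, not zα alone. That is correct in principle. To turn 2.576 into 2.325, however, the alternative SD would have to exceed the null SD by about 11% (2.576/2.325 = 1.108), and by nearly the same amount in all 18 rows although the effects differ widely. The article itself assumes equal variance.

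Thirdly, a normal approximation with SD equal to the control mean gives 2384/2664/3038 at 2-sided .01, within 3% of the planning row, and 82% power at 2500. It matches only 19 of the 54 cells, misses others by up to about 23% (520 against 424), and has the wrong column ratios.

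Finally, recruitment is complete, type I error control is untouched, and LOS may be tested at .05. All true, which is why the remedy is confined to the reported figures. The article does not say that its judgement of adequate power for splitting α, made at the final interim analysis, rested on Table 2, so no conclusion is drawn about that judgement.

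**Conclusion.** The concern holds. Table 2's numbers do not belong to the α in its title, and the power claim for LOS is wrong as written. On the table's own model, 2500 patients give about 75% power at 2-sided .01, against 82.6% at the α the table actually fits. The trial is about 242 patients short of 80% (2742 − 2500). Where .05 is passed on from acute hospital care, power is about 90%.

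The mismatch in α rests on the usual (zα + zpower)² scaling and is confirmed by the cell-by-cell match under exponential LOS. The documents do not show whether the label or the calculation departs from what the sponsor intended. Either way, the power for the test as specified is overstated.

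**What to change.** Confirm from the original calculation which α, sidedness and LOS distribution were used, and state them. Then:

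- Replace the power sentence: on the model behind Table 2, 2500 patients give about 75% power for LOS at 2-sided α=.01, and about 90% if LOS is tested at .05.
- Either recompute Table 2 at 2-sided .01 (multiply the 80, 85 and 90% columns by 1.164, 1.154 and 1.143) or relabel it as 1-sided .01, equivalent to 2-sided .02. If it is relabelled, the 75% must still be given, because the analysis uses a 2-sided test at .01.
- Make the matching correction in the Discussion, where the trial is described as powered for a one-day reduction in at least 35% of patients.

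The cost is a corrected table or label and a few corrected sentences. The stated power becomes less favourable. No patients are added, and neither the test nor the fallback rule changes.
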